### Sample size calculation

We calculated the necessary sample size for each of our two subsamples (intervention and control) with the G*Power Analysis software program for two-sample t-tests [17], and by reference to our primary outcome measure (pain intensity). Based on the results of our pretests, we expected a small to medium effect of 0.4 for the comparison of the two groups (with an alpha level = 0.05, two tailed, β = 0.2). Results indicate that at least 93 participants are required for each group, for a total of 186.

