### Statistical analysis

Descriptive statistics will be used to describe the characteristics of the study sample. Analysis of variance will be used for the evaluation of the changes of the continuous outcomes pain intensity and physical functioning (T1-T2, T1- T3). Research condition (attachment style and study group), will be used as independent variable. Demographic variables such as sex, age, education and clinical variables such as opioid intake and comorbidity will be entered as covariates. Partial regression coefficients will be used to determine if the “working alliance” mediates the effect of attachment on the continuous outcomes (pain and physical functioning).

Missing data on the questionnaires will be handled according to the questionnaire protocol.

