## Conclusions

### Trial status

Recruitment of patients for the control group started in March 2012. Pre- and post-treatment assessments were complete by Oct. 2013 with a total of 184 patients who received a questionnaire at T1 (for an overview of the recruitment process including dropout numbers, see Fig. 3). The 6-month follow-up questionnaires of the control group were completely sent out by May 2014. Each team member received monthly intervention training sessions between Nov. 2013 and May 2015. For an overview of the received attachment training, see Table 2. Recruitment of patients for the intervention group started in March 2014. Pre- and post-tretments were complte by Dec. 2015 with a total of 194 patients who received T1. The 6-months follow-up questionnaires of the interventions group will be completely sent out by June 2016.

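### The only missing-data rule cannot deal with an unreturned T2 or T3 form, so the change-score ANOVA as written compares only the patients who returned that form

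*Protocol article*

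**What the plan says.** All of this comes from the protocol article.

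- **Analysis** (Statistical analysis): "Analysis of variance will be used for the evaluation of the changes of the continuous outcomes pain intensity and physical functioning (T1-T2, T1- T3"). Study group and attachment style are the independent variables; demographic and clinical variables are covariates.
- **Missing data** (same section): "Missing data on the questionnaires will be handled according to the questionnaire protocol". The article gives no other rule on missing data.
- **Sample size** (Sample size calculation): "at least 93 participants are required for each group", 186 in total. No allowance for dropout is stated.
- **Numbers at T1** (Trial status): controls "with a total of 184 patients who received a questionnaire at T1", intervention block "with a total of 194 patients who received T1". Dropout numbers are referred to Fig. 3, which cannot be read here. T3 is described only in terms of questionnaires sent out; the text counts no returned T2 or T3 forms.
- **Design** (Design): two consecutive blocks, not randomised.

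**The concern.** The stated rule and the stated outcome do not fit each other. A questionnaire's scoring instructions say what to do when a returned form has blanks. A change score needs two returned forms, and no scoring instruction creates the second. The mismatch is sharpest for pain intensity, the outcome on which the trial was sized: each visual analogue scale is a single mark, so there are no sibling items to prorate from.

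Two things are at stake. First, each contrast would rest on whoever returned that form, so the T1-T2 and T1-T3 results may describe different sets of patients. If return is related to outcome, and differently so in the two blocks, the group effect is biased on top of any imbalance from the non-randomised sequence. Second, information is thrown away: a T2 value predicts T3, but a patient with T2 and no T3 adds nothing to the T3 comparison.

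**Working it through.** **1. The plan's own figure.** Inputs from Sample size calculation: "we expected a small to medium effect of 0.4 for the comparison of the two groups", "with an alpha level = 0.05, two tailed, β = 0.2", and a two-sample t-test.

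Normal approximation: n per group = 2 × (1.960 + 0.842)² / 0.4² = 98.1, so 99. The exact t-test gives 99.08, so 100 per group. The stated 93 does not reproduce: it has power 0.774 at d = 0.4 and would match d = 0.413. That is a separate matter; both 93 and 100 are carried below. The total of 186 is 2 × 93, without inflation for dropout.

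**2. Who enters which contrast under the rule as written.**

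| Forms returned | T1-T2 change | T1-T3 change |
|---|---|---|
| T1, T2, T3 | yes | yes |
| T1, T2 | yes | no; the T2 value is unused for T3 |
| T1, T3 | no | yes |
| T1 only | no | no |

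**3. Loss that the T1 numbers could absorb.**

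- To fall to 93: 1 − 93/184 = 49% (control); 1 − 93/194 = 52% (intervention).
- To fall to 100: 1 − 100/184 = 46%; 1 − 100/194 = 48%.

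These are tolerances, not observed losses.

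**4. Power is not the main issue.** With d = 0.4 and an assumed equal loss from 184 and 194:

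| Loss (assumed) | Remaining | Power |
|---|---|---|
| 0% | 184 / 194 | 0.97 |
| 20% | 147 / 155 | 0.93 |
| 40% | 110 / 116 | 0.85 |
| 50% | 92 / 97 | 0.78 |
| 60% | 74 / 78 | 0.69 |

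**5. Bias.** In one block let p be the share lost, R the mean outcome of returners and N that of non-returners. The full-block mean is (1 − p)R + pN, so the returner mean is off by R − [(1 − p)R + pN] = p(R − N). With the same p in both blocks, and gaps R − N that differ between blocks by g SD, the group difference is off by p × g.

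| p (assumed) | g = 0 | g = 0.3 SD (assumed) |
|---|---|---|
| 0.2 | 0 | 0.06 SD |
| 0.4 | 0 | 0.12 SD |

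For example, with p = 0.4 and non-returners 0.5 SD worse in controls but 0.2 SD worse in the intervention block, the returner means flatter the blocks by 0.4 × 0.5 = 0.20 and 0.4 × 0.2 = 0.08 SD. The intervention effect is then understated by 0.12 SD; swapping the gaps overstates it by as much. Against the planned effect of 0.4, 0.06 is 15% and 0.12 is 30%.

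**The case against.** The strongest reply is that this is an omission. A condensed article commonly leaves missing visits, analysis sets and sensitivity analyses to a fuller plan, and none is shown. The quoted sentence speaks of questionnaires and does not claim to cover dropout; nowhere does the article say that non-returners are excluded or that the two changes get separate ANOVAs. It is fair that both are inferences. But the article does fix the form of the outcome and does name a missing-data rule, and a change score cannot be formed without the later form. The point is the misfit between two stated elements, and it stands.

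Other replies succeed against stronger readings:

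- A reader might infer heavy attrition from about twice the target at T1 and a figure on dropouts. The text does not support that. The counts are of patients given T1, no completer numbers are readable, and the surplus fits over-recruitment or enrolment over a fixed period just as well.
- A reader might infer non-random loss from Potential limitations, which says that preoccupied and fearful patients benefit least. That concerns benefit, not who returns forms. Attachment style is also measured at T1 and is a factor in the planned ANOVA, so loss that depends on style alone need not bias the group effect within styles.
- The bias figures are assumptions and use unadjusted means. With equal loss and equal gaps the bias is zero; the relevant g is what remains after attachment style and covariates are accounted for.
- A mixed model rests on its own untestable assumption.

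**Conclusion.** The concern holds in a limited form. As written, the missing-data rule does not serve the change-score analysis: each contrast falls back on returners, and T2 data of patients lost at T3 are not used for T3. This does not depend on the dropout rate.

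The consequence cannot be sized from the documents. Under assumed equal loss of 20% to 40% and gaps differing between blocks by 0 to 0.3 SD, the bias runs from 0 to 0.12 SD. The T1 numbers give no protection against this: the target would still be met with about half of each block gone, so meeting it says nothing about selection. The documents do not show that attrition was heavy, that it was related to outcome, or that it differed between the blocks. This is a cheap improvement to the analysis, not evidence that the results are biased.

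**What to change.** Analyse each primary outcome with one linear mixed model in which T2 and T3 are repeated responses. Include the T1 value, study group, attachment style, visit, group × visit, group × attachment style and the covariates already planned, and use every patient with T1 and at least one later form. Attachment style must stay in as a factor, because the hypotheses attribute the benefit mainly to insecurely attached patients. Report the T2 and T3 group contrasts from this model.

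For patients with neither later form, use multiple imputation from T1 variables, including attachment. Keep the change-score ANOVA on returners as a sensitivity analysis. State that the questionnaires' own rules apply to item-level gaps only.

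The cost is revised wording and modest extra programming, with no new data. When the article was written, the intervention block's follow-up forms were still being sent out, so the change could precede the final analysis. The downside is a missing-at-random assumption given T1, T2 and the covariates: the model does not remove bias from loss that depends on unobserved outcomes.

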### Intervention

By drawing on attachment theoretical ideas, we do not mean to change any of the overall aims of multimodal pain treatment. Also, it would be unrealistic to aim at a complete reversal of underlying insecure attachment patterns to a secure pattern in such a setting.

Rather, we aim at an improvement of the therapeutic alliance (a) in terms of the therapists’ general ability to provide a secure base for his patients, and (b) in the therapists’ ability to understand and deal with their patients’ individual attachment-based motivations and needs. Thus, the intervention’s guidelines should help facilitate the attainment of the program’s aims by enhancing the patient’s sense of having a secure base. Therefore, our intervention training includes both general directions for building a meaningful therapeutic relationship, and guidelines, which are specifically tailored to the needs of individual attachment styles.

To develop general guidelines for an improvement of the working alliance, we identified as useful starting point the therapeutic approach of the complementary therapeutic relationship. This approach emphasizes the underlying motives (such as the attachment motive) of patients [9, 48].

We also developed more specific guidelines for each attachment style based on a further development of existing literature on the application of attachment ideas to specific therapeutic settings. For example, attachment theoretical ideas have been incorporated in therapeutic programs for the treatment of borderline personality disorder, depression, medically unexplained symptoms, family and couple therapy [3, 13, 25, 28, 29]. A multimodal rehabilitation program for children and adolescents with functional impairment in Australia applies for instance attachment principles to their family-based intervention [29, 30]. However, as guidelines often remain vague, are tailored to one specific therapeutic school or are given on the assumption of a long-term therapy, all of which is not suitable for our context, we only used them as a starting point.

For example, patients with preoccupied attachment styles might benefit more from an initially concordant approach which puts emphasis on the therapist’s role as a secure base. Patients with preoccupied or fearful attachment styles might feel overwhelmed by a program which is too fast in emphasizing autonomy, and possibly reinforce existing fears of rejection and abandonment. On the other hand, dismissively attached patients might feel uncomfortable with high levels of proximity, and the amount of guidance and care preoccupied patients favor to feel safe.

The multimodal setting requires an attachment-based concept, which can be employed by medical personnel with diverse professional backgrounds such as doctors, physiotherapists, occupational therapists, music and dance therapists. Additionally, therapists may avail themselves of diverse methodological approaches such as psychoanalytical or cognitive behavioral therapy.

Each team member is provided with a manual of the general guidelines and the attachment style-specific guidelines. In the course of data collection for the intervention group, these guidelines will also be constantly extended.

### Measures

#### Psychopathology

The Structured Clinical Interview for DSM-IV Axis I Disorders (SCID-I; [54]) is a semi-structured interview for assessing DSM-IV Axis I diagnoses. It is considered diagnostic gold standard in psychiatric assessment, and has shown high reliability and superior validity when conducted by trained health professionals.

#### Demographic information, help-seeking behavior and use of medication

Items are adapted from the German Pain Questionnaire. The German pain questionnaire (DSF; [42]) has been developed and validated by the International Association for the Study of Pain (DGSS). The concept of the DSF is based on a bio - psycho - social pain model. The modular approach to pain assessment consists of: demographic data, pain variables (e. g. pain sites, temporal characteristics, duration, intensity), pain associated symptoms, affective and sensory qualities of pain (adjective list by Geissner, SES Copyright, [23]), pain relieving and intensifying factors, previous pain treatment procedures, pain-related disability (Pain Disability Index by [49]), depression test CES-D (Center for Epidemiological Studies Depression Test), comorbid conditions, social factors (educational level, occupation, retirement status, compensation and/or litigation status, disability for work),health related quality of life (SF-36 Copyright).

#### Attachment style

Assessments of both intervention group and baseline group are identical. For an overview of all measures at T1, T2, and T3, see Table 1. Patients’ attachment patterns will be assessed with the help of the relationship questionnaire (RQ 2; [2]) and the revised Experience of Close Relationships questionnaire [15] in its newly developed German short version [6, 15] . The ECR-RD 12 has been anchored in two different ways to assess the two regulatory attachment strategies *avoidance* and *anxiety* (a) specifically with regard to partners or spouses and (b) more globally with regard to friends and relatives. The original version of the ECR-R [20] was based on the principles of item response theory and specifically assesses attachment representations in romantic relationships (e.g. attachment anxiety: ‘I find that my partner/partners doesn’t/don’t want to get as close as I would like’; attachment avoidance: ‘I find it difficult to allow myself to depend on romantic partners’).

**Table 1 Tab1:** Overview of variables and instruments

Domain	Instruments	T1	T2	T3
Psychological disorders, axis 1	*German semi-structured Clinical Interview* based on DSM-IV (SKID-I)	**×**		
Socio-demographic variables	Items adapted from the *German Pain Questionnaire*	**×**		
Help-seeking behavior	Items adapted from the *German Pain Questionnaire*	**×**		**×**
Use of Medication	Items adapted from the *German Pain Questionnaire*	**×**		**×**
Attachment Patterns	•* Relationship Questionnaire* (RQ 2) •* Experience of Close Relationships* (ECR-RD 12) with regard to a) partner/spouse b) friends/relatives	**×**		**×**
Pain	•* Pain Intensity* **:** Visual Analogue Scales (VAS) • *Pain Frequency*: number of days with pain, number of days with strong pain (previous month)	**×**	**×**	**×**
Physical Functioning	• *Oswestry Disability Index* (ODI) •* Health Survey* (SF12)	**×**	**×**	**×**
Emotional Distress	•* Depression, Anxiety and Stress Scale* (DASS) •* Health Survey* (SF12)	**×**	**×**	**×**
Interpersonal Problems	*Inventory of Interpersonal Problems* (IIP 32)	**×**	**×**	**×**
Self-esteem	*Rosenberg Self Esteem Scale* (RSES)	**×**	**×**	**×**
Coping	*Coping Strategies Questionnaire* (CSQ-D)	**×**	**×**	**×**
Evaluation of Therapeutic Process	•* Working Alliance Inventory* (WAI) •* Therapie Stations-Erfahrungs-Bogen* (TSEB)		**×**	

*T1, before treatment; T2, after treatment; T3, six months follow-up*

The ECR-RD has shown high levels of test-retest stability and discriminant validity [47]. We decided to include both an assessment of attachment styles and attachment dimensions to enhance measurement precision and hereby facilitate the interpretation of results. The brief self-report RQ 2 captures a person’s dominant (cognitive) schematic representation of self and others. It consists of four short paragraphs, each describing one attachment pattern (e.g. the fearful prototype reads, ‘I am uncomfortable getting close to others. I want emotionally close relationships, but I find it difficult to trust others completely, or to depend on them. I worry that I will be hurt if I allow myself to become too close to others’). The participants is then asked to rate their degree of correspondence to each prototype on a 7-point Likert-type scale ranging from 1 (completely true) to 7 (completely false). The therapeutic team will be informed about the results only in the treatment condition. In this way, treatment can be tailored to each patient’s specific attachment needs.

From these four prototype ratings, the ‘model of self’ and the ‘model of other’ scales were calculated as proposed by the authors. Patients with positive models of both self and other were classified as ‘secure’, patients with negative/neutral models for both as ‘fearful’, and individuals with mixed results as ‘preoccupied’ or ‘dismissing’. The RQ-2 has been shown to have an acceptable level of psychometric soundness as a brief screening instrument, and it is relatively independent from self-deceptive biases. The RQ-2 implemented has been used in multiple international studies and proved to be an efficient screening instrument with good construct validity across cultures.

### Primary outcome measures

With two Visual Analogue Scales, we assess the pain intensity at present and within the previous week. Patients are also asked to indicate the number of days they experienced pain, and the number of days they experienced strong pain, both within the previous month. Physical functioning will be assessed with the Oswestry Disability Index by Mannion et al. [34], which has been specifically developed for use with pain patients. Also, we included a widely used German short version of the Health Survey to assess physical functioning and health-related quality of life more generally [8].

#### Pain intensity and functional impairment

Subjective pain intensity over the preceding week was measured on a visual analogue scale (VAS; [26]) ranging from 0 (no pain) to 100 (worst imaginable pain). Each patient indicated a position on the VAS in response to the question “How severe was your pain on average in the last seven days?” The VAS is a valid and reliable instrument for measuring the intensity of pain.

#### Physical functioning

The validated Oswestry Disability Index (ODI; [16]) is currently considered by many as the gold standard for measuring degree of disability and estimating quality of life in a person with low back pain. The self-completed questionnaire contains ten topics concerning intensity of pain, lifting, ability to care for oneself, ability to walk, ability to sit, sexual function, ability to stand, social life, sleep quality, and ability to travel.

#### Emotional distress

The Depression Anxiety Stress Scales (DASS; [33]) is made up of 42 self-report items, each reflecting a negative emotional symptom. Each of these is rated on a four-point Likert scale of frequency or severity of the participants' experiences over the last week with the intention of emphasising states over traits. These scores ranged from 0, meaning that the client believed the item "did not apply to them at all", to 3 meaning that the client considered the item to "apply to them very much, or most of the time". It is also stressed in the instructions that there are no right or wrong answers. The main purpose of the DASS is to isolate and identify aspects of emotional disturbance; for example, to assess the degree of severity of the core symptoms of depression, anxiety or stress.

The SF-12 Health Survey [7] is a shorter version of the SF-36 Health Survey that uses just 12 questions to measure functional health and well-being from the patient’s point of view. Taking only two to three minutes to complete, the SF-12 is a practical, reliable and valid measure of physical and mental health and is particularly useful in large population health surveys or for applications that combine a generic and disease-specific health survey.

#### Interpersonal problems and self-esteem

The inventory of Interpersonal Problems (IIP 32; [27, 50]) is a self-report instrument that identifies a person's most salient interpersonal difficulties. The items provide representative interpersonal problems that are commonly reported in initial interviews.

The Rosenberg Self-Esteem Scale [44], a widely used self-report instrument for evaluating individual self-esteem, was investigated using item response theory. Factor analysis identified a single common factor, contrary to some previous studies that extracted separate Self-Confidence and Self-Depreciation factors. A 10-item scale that measures global self-worth by measuring both positive andnegative feelings about the self. The scale is believed to be uni-dimensional. All items are answered using a 4-point Likert scale format ranging from strongly agree to strongly disagree.

#### Coping

Coping strategies in the context of chronic pain refer to the way individuals who experience pain develop ways to tolerate, minimize or reduce their pain. The Coping Strategies Questionnaire (CSQ; [52]) is internationally the most widely used measure of pain coping strategies. The value of the CSQ is its ability to assess various cognitive and behavioral coping factors derived from a rationally constructed pool of strategies reported by patients experiencing pain and cross-validated by pain clinicians and pain psychologists. It identifies both active and passive coping strategies.

#### Evaluation and therapeutic process

The Working Alliance Inventory-Short Revised (WAI-SR; [53]) is a recently refined measure of the therapeutic alliance that assesses three key aspects of the therapeutic alliance: (a) agreement on the tasks of therapy, (b) agreement on the goals of therapy and (c) development of an affective bond.

The German Stations-Erfahrungs-Bogen [45] is an instrument for the process evaluation inpatient psychotherapy. Application possibilities are in the clinical area, in science as well as in the quality monitoring of the treatment facility. The TSEB is a patient questionnaire for the assessment of experiencing inpatient psychotherapy. With 38 items, the self-assessment of patient regarding the following subscales is applicable: relationship to therapeutic team, relationship with the therapist, emotional atmosphere between the patient, need for affection by the other patients, experiencing the intensity of treatment, experience the therapeutic framework and self-efficacy (e.g. relationship with therapist: ‘I found it easy to connect with my therapist’).

